It is requisite that each neurological event be allocated to a subcategory as follows:A transient ischemic attack can be defined as an abrupt episode of neurological deficit that is fully reversible within a 24 h period and does not demonstrate evidence of infarction on imaging studies.A cerebrovascular accident, or CVA, is a medical term used to describe either an ischemic or hemorrhagic stroke. Ischemic stroke is defined as a condition with a duration of more than 24 h, while hemorrhagic stroke is characterized by the occurrence of infarction on imaging. In the event of hemorrhagic conversion following an ischemic stroke, the classification remains consistent.Toxic metabolic encephalopathy (TME) is a condition characterized by impaired brain function resulting from disrupted systemic metabolism or exposure to external agents. It presents with altered levels of consciousness and awareness, as well as a lack of focal neurological signs and a negative brain scan.Other.Renal events.

The assessment of renal function will be categorized in accordance with the predicted glomerular filtration rate (eGFR), which will be determined through the application of both the Chronic Kidney Disease Epidemiology Collaboration (CKD-EPI) equation [39] and the European Kidney Function Consortium (EKFC) equation [40]. The extent of renal failure will be classified into different stages, as detailed in Table 6.

Two distinct categories of kidney-related events will be identified and defined:○Renal dysfunction.

Abnormalities in kidney function will be characterized by a rise in serum creatinine (Cr), exceeding 100% from the established baseline, and a Cr concentration exceeding 2.0.

○Renal failure.

A new criterion has been established for the initiation of hemodialysis in patients with renal dysfunction. It should be noted that the aforementioned definition excludes aquapheresis procedures that are solely intended for the removal of excess fluid volume.

Hepatic dysfunction.

Hepatic dysfunction is diagnosed when any two liver tests (total bilirubin, aspartate aminotransferase/AST, and alanine aminotransferase/ALT) exceed the upper normal limit by threefold. It is also diagnosed as the primary cause of death if liver dysfunction is identified.

Respiratory insufficiency.

The inability to discontinue ventilatory support within 48 h after surgery, which necessitates re-intubation or tracheostomy, is indicative of respiratory function impairment. This definition does not pertain to instances where the patient is re-intubated for a further surgical procedure or where the patient is temporarily intubated for diagnostic or treatment purposes.

Bleeding.

An incident characterized by bleeding is any instance where one of the following occurs.

○The transfusion of more than 10 units of red blood cells within the initial 24 h period following surgery has been identified as a potential risk factor for death due to hemorrhage.○In cases of hemorrhage or tamponade, reoperation may be required.

NOTE: A hemorrhagic stroke is categorized as a neurological incident, separate from the occurrence of bleeding.

Pericardial fluid trapping.

The term “pericardial fluid accumulation” denotes the accumulation of either fluid or thrombus within the area of the pericardium. In instances where surgery or percutaneous catheter drainage is deemed necessary, this diagnosis must be made. The aforementioned event may be classified further into two categories: firstly, those instances that present with the clinical signs of tamponade, such as an increased central venous pressure and a decreased cardiac output, and secondly, those that do not present with these signs of tamponade.

Arterial non-CNS thromboembolism.

A definitive assessment of an acute systemic arterial perfusion deficit in any non-cerebrovascular organ system resulting from thromboembolism can be achieved through the confirmation of one or more of the evidence-based criteria outlined below:○The patient was subjected to standard clinical and laboratory examinations, as well as an operative evaluation of the relevant findings.○Findings from the postmortem.

The provided delineation does not include occurrences pertaining to the neurological domain.

Wound dehiscence.

The surgical incision has been compromised as a result of an event that did not involve infection. This necessitates surgical repair.

Venous thromboembolic event.

The presence of a venous thromboembolic event, such as deep vein thrombosis or pulmonary embolism, can be identified through the utilization of established diagnostic techniques.

•Other.▪A critical incident is defined as a clinically significant alteration in the patient’s health state, an event resulting in death, permanent disability, or hospitalization, or an increase in the length of hospitalization. Supplementary Tables S1–S3 in Supplementary Material [41].

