An adverse event (AE), as defined by the International Council for Harmonisation of Technical Requirements for Pharmaceuticals for Human Use (ICH), is any event that occurs during a clinical trial and that results in any of the following: a change in the condition of the study participant; a change in the participant’s status; or a new disease or syndrome that the participant develops. An adverse event must be considered clinically significant. Furthermore, it must occur in a participant who is taking part in the trial, regardless of whether the event is related to the study intervention. A pre-existing pathological state will only be designated as an adverse event if there is a discernible alteration in its character, severity, or degree.

A comparison will be made between the two groups with respect to the occurrence of any adverse effects that are deemed to be significant throughout the period of the experimental trial. The onus for adjudicating all serious and protocol-defined adverse events (AEs) will be borne by the clinical control specialists responsible for overseeing this study at each research center. Adverse events will be documented in accordance with specified safety endpoints. The report will provide detailed information on the incidence and prevalence of serious adverse effects, including the frequency of each adverse occurrence, the incidence rate per patient per annum, and the temporal distribution of adverse events. Moreover, the incidence of patients presenting with each discrete category of serious adverse event will be recorded. Safety metrics will be gathered throughout the duration of the patient follow-up period. Subsequently, the incidence of each event type will be calculated with 95% confidence intervals in alignment with the specified safety endpoints.

○Serious adverse event.

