A total sample population of 630 patients was calculated as sufficient to detect a significant difference in the rate of reverse left ventricular remodeling, with 384 patients undergoing surgical mitral valve repair and 246 patients undergoing transcatheter mitral valve repair. This study was powered at 80% with a two-tailed alpha level of 0.05. In order for a *p*-value to be deemed statistically significant, it must be less than 0.05. All statistical analyses were performed with the aid of the R software package developed by the R Foundation for Statistical Computing in Vienna, Austria.

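### The respiratory insufficiency definition ties re-intubation and tracheostomy to failed weaning at 48 h instead of listing them as alternatives, so some events are missed and centres may classify the same record differently

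*Protocol article*

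**What the plan says.** The definition is in the protocol article, section 2.3, under Specific Adverse Event Definitions, Respiratory insufficiency. It has two sentences.

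- The first opens with "The inability to discontinue ventilatory support within 48 h after surgery" and, picking up at its last two words, reads on "after surgery, which necessitates re-intubation or tracheostomy, is indicative of respiratory function impairment".
- The second is an exclusion: "This definition does not pertain to instances where the patient is re-intubated for a further surgical procedure". It also removes temporary intubation done for diagnosis or treatment.

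The next definition, Bleeding, is built differently: "An incident characterized by bleeding is any instance where one of the following occurs".

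The Adverse events text in the same section says how such events are used. The two groups are compared on serious adverse events, and "the incidence of each event type will be calculated with 95% confidence intervals in alignment with the specified safety endpoints". Serious and protocol-defined events are adjudicated by specialists at each research centre. Table 3 lists five centres.

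**The concern.** A safety event should be defined so that two people reading the same chart reach the same answer. This sentence has one head condition, failure to stop support by 48 h, and hangs re-intubation or tracheostomy on it with a relative clause. It does not say whether that clause adds a second requirement or only describes what tends to follow. It also gives no route by which re-intubation counts by itself.

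The incidence of this event is to be reported with a confidence interval and set against the other arm. A definition that misses part of the complication gives too low a rate, and one that is read in two ways gives a rate that depends on which centre adjudicated. The surgical arm includes operations on cardiopulmonary bypass, so it is plausible that more of the affected patients are there. In that case the comparison would tend to understate respiratory harm after surgery relative to TEER.

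**Working it through.** **Step 1. The readings.** The article states no figure for this event, so there is nothing to reproduce. The check is of the sentence's logic.

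- *Conjunctive*: support not stopped by 48 h AND re-intubation or tracheostomy.
- *Consequence*: support not stopped by 48 h; the clause only describes what follows.
- *Alternatives* (not what is written): support not stopped by 48 h OR re-intubation OR tracheostomy.

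**Step 2. Four constructed records.**

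| Record | Conjunctive | Consequence | Alternatives |
|---|---|---|---|
| A. Ventilated 96 h, then extubated | no | yes | yes |
| B. Off at 8 h, re-intubated at 30 h for respiratory failure, off at 40 h | no | no | yes |
| C. Ventilated beyond 48 h, then tracheostomy | yes | yes | yes |
| D. Off at 8 h, re-intubated at 30 h, still supported past 48 h | yes | yes | yes |

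Record B is missed on both literal readings. Record A separates them, and it is where two centres could disagree while both follow the text.

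**Step 3. The two sentences side by side.** The second sentence removes re-intubation for a further operation. That carve-out is mainly needed if re-intubation can qualify by itself, and the first sentence does not let it. A patient who never comes off the ventilator also cannot be re-intubated in the usual sense. So on the conjunctive reading the re-intubation route works only for records like D.

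**Step 4. Direction.** Let a = P(support not stopped by 48 h), b = P(re-intubation or tracheostomy) and c = P(both).

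- Conjunctive count = c
- Consequence count = a
- Alternatives count = a + b − c

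Since c ≤ a ≤ a + b − c, neither literal reading can exceed the alternatives count.

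**Step 5. Size, for illustration only.** The article gives none of a, b or c, so all three are assumed. Share missed is 1 − c/(a + b − c) on the conjunctive reading and (b − c)/(a + b − c) on the consequence reading. Overlap is c as a share of the smaller of a and b.

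| a, b | Overlap | c | a + b − c | Missed, conjunctive | Missed, consequence |
|---|---|---|---|---|---|
| 5%, 3% | half | 1.5% | 6.5% | 77% | 23% |
| 10%, 5% | none | 0% | 15% | 100% | 33% |
| 10%, 5% | half | 2.5% | 12.5% | 80% | 20% |
| 10%, 5% | full | 5% | 10% | 50% | 0% |
| 10%, 10% | none | 0% | 20% | 100% | 50% |
| 10%, 10% | full | 10% | 10% | 0% | 0% |

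Section 3 plans the groups "with 384 patients undergoing surgical mitral valve repair and 246 patients undergoing transcatheter mitral valve repair". At a = 10%, b = 5% and half overlap, the 384 surgical patients would give 384 × 0.025 = 9.6 events on the conjunctive reading, 384 × 0.10 = 38.4 on the consequence reading and 384 × 0.125 = 48.0 as alternatives. The gap between the two literal readings is 28.8 patients from the same charts.

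**The case against.** A reader might infer that the definition simply requires both elements and that the event is therefore heavily under-counted. The article does not support that.

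- **Requiring both is only one reading.** A comma followed by a relative clause can describe a consequence. Record A then counts, and only records like B are lost.
- **The size rests wholly on assumptions.** Suppose 5–10% are ventilated beyond 48 h, 10–25% of these go on to tracheostomy or re-intubation, and a further 2–4% are re-intubated after early extubation. The conjunctive count is then 5 × 0.10 = 0.5% against 5 + 2 = 7%, or 10 × 0.25 = 2.5% against 10 + 4 = 14%, a loss of 93% or 82%. With the same inputs the consequence reading loses only 2/7 or 4/14, about 29%. No rate in the article favours either figure.
- **The exclusion does not prove intent.** It also has work to do on the conjunctive reading: a patient still supported past 48 h whose re-intubation was for a second operation would meet both elements and is removed by it. It hints that re-intubation alone was meant to count, and no more.
- **Some missed cases surface elsewhere.** Life-threatening events and protracted hospitalization are serious adverse events, the Other category covers longer hospitalization, and ICU days are recorded. Supplementary Tables S1–S3 are not shown and might add criteria.
- **The bias between arms is not documented.** The article gives no ventilation practice or respiratory event rate by arm.

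These points stand, and they limit the claim to ambiguity plus an under-count of unknown size. They do not rescue record B, which is outside the text on either reading, and cases caught under another heading are still absent from the respiratory incidence. The event is also one of many: neither the primary endpoint (LVEDVI) nor the main secondary endpoint (all-cause mortality) depends on it.

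**Conclusion.** The definition is faulty as written. Re-intubation for respiratory failure after early extubation, with support off again by 48 h, is not an event on any literal reading. Prolonged ventilation without re-intubation or tracheostomy is not an event on the conjunctive reading. The first sentence sits badly with its own exclusion, and local adjudication at five centres leaves room for inconsistent classification.

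The direction follows from the logic alone: measured against a list of alternatives, any error is an under-count. The size cannot be derived from the documents; the percentages above depend on assumed rates and overlap and on which reading is taken. A larger effect in the surgical arm is plausible but not shown. The point merits correction because a reported safety rate depends on it and the repair is cheap. It does not threaten the main analyses.

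**What to change.** Reconcile the two sentences by listing the article's own elements as alternatives: ventilatory support not discontinued within 48 h, OR re-intubation, OR tracheostomy. Keep the existing exclusions. When doing so, make clear that the exclusion for temporary intubation for treatment does not reach re-intubation for respiratory failure, or it could cancel the new criterion. State that the same rule applies in both arms and at all centres. If the sponsor instead means the elements to be jointly required, the text should say so and the exclusion should be reworded to match.

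The cost is one sentence of text and, where records were already adjudicated, a second look at those with prolonged support or re-intubation. The real downside is specificity: a list of alternatives takes in milder cases, such as a short re-intubation. Reporting the three components separately beside the total would let readers see that mix.

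### As worded, the arterial non-CNS thromboembolism definition leaves out an embolus shown by clinical, laboratory or imaging findings in a living patient who is not operated on

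*Protocol article*

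**What the plan says.** All of this stands in section 2.3 of the protocol article, under Safety and Specific Adverse Event Definitions.

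- **The event.** The entry headed "Arterial non-CNS thromboembolism" concerns an "acute systemic arterial perfusion deficit in any non-cerebrovascular organ system resulting from thromboembolism".
- **The rule.** A definitive assessment "can be achieved through the confirmation of one or more of the evidence-based criteria outlined below".
- **First criterion.** "The patient was subjected to standard clinical and laboratory examinations, as well as an operative evaluation of the relevant findings".
- **Second criterion.** "Findings from the postmortem".
- **A neighbouring entry.** A venous thromboembolic event "can be identified through the utilization of established diagnostic techniques". No operation or autopsy is mentioned.
- **Use in the analysis.** The Adverse events text says that significant adverse effects will be compared between the two groups and that "the incidence of each event type will be calculated with 95% confidence intervals". Adjudication is done by specialists at each centre.
- **The residual category.** Under Other, a critical incident includes "an event resulting in death, permanent disability, or hospitalization, or an increase in the length of hospitalization".

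**The concern.** The two criteria are alternatives, but the first is one bullet whose parts are joined by *as well as*. Taken at its word, examination and operative evaluation are both needed. Many arterial emboli outside the brain could be established by clinical, laboratory or imaging evidence without an operation, and the definition gives that evidence no route of its own.

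This matters because one group is surgical and the other transcatheter. If classification depends on whether a patient is operated on or comes to autopsy, the recorded incidence reflects those pathways as well as embolic risk. The weighting in section 3 (Statistical Methods) balances baseline covariates. It does not correct differential classification of an outcome. With adjudication at each centre, an unclear rule may also be read differently across the five sites.

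**Working it through.** The documents give no figure to reproduce, so the check is one of logic.

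**Step 1. Write the definition as a rule.** From the two bullets and the requirement for one or more of them:

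confirmed = (examinations AND operative evaluation) OR postmortem findings

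**Step 2. Apply it to true emboli, under the plain reading and under a looser one in which the first bullet merely lists sources of evidence.**

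| Patient with a demonstrated non-CNS arterial embolus | Plain reading | Looser reading |
|---|---|---|
| Alive, shown by examination, laboratory tests or imaging, no operation | not confirmed | confirmed |
| Alive, examined and operated on, embolus found | confirmed | confirmed |
| Died, embolus found at autopsy | confirmed | confirmed |
| Died, shown before death by examination, laboratory tests or imaging, no operation, no autopsy | not confirmed | confirmed |

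The readings differ only where there is neither an operation nor an autopsy.

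**Step 3. Compare with neighbouring definitions.** Venous thromboembolism rests on diagnostic techniques alone. Endocarditis is sufficiently supported by an echocardiogram showing a new vegetation, with or without other signs. Where wound dehiscence and pericardial fluid are tied to an intervention, the intervention acts as a severity threshold. The arterial entry sets no severity threshold and presents its bullets as proof of diagnosis. Nothing in the text explains why arterial emboli should need an operation.

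**Step 4. Trace the effect on the reported figures.** Let c be the share of true emboli in a group that meet the rule, and assume that every confirmed case is a true one. Then:

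- recorded incidence = true incidence × c
- recorded ratio (surgery to TEER) = true ratio × c(surgery) / c(TEER)

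If c is below 1, the recorded incidence is too low. If c is the same in both groups, the ratio is preserved. If c differs, the ratio moves. The documents give no value for c in either group.

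**Step 5. Check what else depends on this category.** The primary endpoint is LVEDVI at 10 years (section 2.2.1) and the main secondary endpoint is all-cause mortality (section 2.2.2). The MACE components are death, stroke, mitral valve re-intervention, worsening heart failure and CHF hospitalization. None of these uses this definition.

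**The case against.** The strongest defence is that the text does not say *only*. An assessment that *can* be achieved in certain ways is permissive wording, and *as well as* may have been meant as a list of evidence sources. The section uses that phrase both ways: as a plain list under neurologic dysfunction, and conjunctively for toxic metabolic encephalopathy. Adjacent entries are also loosely phrased, so poor drafting is at least as likely as a deliberate choice to require an operation. This stands in part. The wording is ambiguous, and a reader should not infer a stated exclusion rule. But two bullets under a one-or-more rule favour the conjunctive reading, and if the looser meaning was intended, separate bullets are still the remedy.

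It is also fair that such cases need not vanish. A case that meets the serious adverse event definition, or the critical-incident definition under Other, is still recorded. The loss is from this category, not from the safety data as a whole.

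The Supplementary Tables S1–S3, to which the definitions refer, are not shown. Whether they add to this entry cannot be checked.

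Two stronger readings are tempting, and the documents support neither.

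- **That a negative work-up plus an operation would count as an event,** because the first bullet describes tests done and no result. The governing sentence already requires confirmation of a perfusion deficit caused by thromboembolism, and the bullet speaks of relevant findings. A negative work-up confirms nothing of that kind.
- **That equal risk would appear as a 2.5-fold difference.** That needs assumed shares of 50% confirmed after surgery and 20% after TEER (0.50/0.20 = 2.5). Equal shares give 1.0 and reversed shares give 0.20/0.50 = 0.4. With no rates in the documents, none of these can be preferred.

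**Conclusion.** The point holds as a minor correction to one safety category. On its plain reading, the definition does not classify a demonstrated embolus as arterial non-CNS thromboembolism when the patient is alive and not operated on. The incidence reported for this category may therefore be understated, and ascertainment may differ between the surgical and TEER groups. Neither the size nor the direction of any difference can be stated.

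This rests on reading the first bullet as conjunctive, and on the unseen supplementary tables not altering the definition. It does not follow that such emboli go unrecorded, or that the comparison favours either group.

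**What to change.** Replace the two bullets with three alternatives, any one of which suffices in both groups:

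- (a) positive clinical, laboratory or imaging findings of the arterial perfusion deficit;
- (b) operative findings;
- (c) postmortem findings.

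Then code the event from the source records in both groups on that basis, including cases filed only as serious adverse events or under Other.

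The cost is one line of the definition and a re-coding of this single event type. No endpoint, sample size or analysis method changes.
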